### Outcome parameters

An overview of the main study outcomes is shown in Figure 1.

#### Body composition

The primary endpoints in this study are changes in whole body composition (fat mass, lean mass, and water) at the end of the fasting intervention as well as 1 and 4 months afterward compared to baseline measured by MRI (44–46) (Figure 3). Furthermore, changes in size and composition of heart (47–52), liver (53, 54), kidney, spleen, adipose tissue, lumbosacral muscle mass, and lower limbs (quadriceps, hamstrings, and calves) (55) over time as well as changes in brain morphometry (56, 57) will be assessed. Details of MRI measurements are provided as Supplementary material.

**FIGURE 3 F3:**
[figure not shown]
Summary of the magnetic resonance imaging/spectroscopy (MRI/MRS) measurements. Body composition after a 12 days fasting period by means of MRI/MRS scans with a focus on the brain **(A)**, liver **(B)**, skeletal muscle **(C)**, and myocardium **(D–F)**. Beyond brain morphometry **(A)**, myocardial mass, function and regional deformation **(F)**, and abdominal organs sizing **(B)** calculated from localized dedicated scans (side panels). Subcutaneous, visceral, extra-visceral and bone marrow fat quantification and total lean mass will be calculated from whole body acquisition (middle panel). MR spectroscopy of the liver **(B)**, leg muscle **(C)**, and heart **(E)** allows complementary fat decomposition, triglycerides and metabolites concentrations quantification. Advanced myocardium tissue characterization will include relaxometry and diffusion parameters mapping, as well as myocardial fiber orientation and local deformation **(D)**. Muscle legs volume and strength (maximum voluntary contraction) will be compared to MRS 31P data and extracted biomarkers of the oxidative metabolism **(C)**.

Changes in bio-electrical multifrequency impedance analysis will enrich the MRI/MRS scans (58–60) with information about global and segmental body composition (water, fat, and lean mass), liquid distribution (total, extracellular, and intracellular water), metabolic indexes [metabolic activity index (MAI)], and protein content (total and active cell mass fraction). Furthermore, the CV fitness will be assessed by measuring maximal oxygen consumption (VO2max) on cycloergometers (61). Triaxial actigraphy will allow a continuous recording of the physical activity and sleep quality during the whole study. Last, we will use standardized morning heart rate variability measurements (Polar H10 with Kubios HRV mobile app.) to assess the autonomous nervous system response along the protocol (62, 63).

#### Lipid function

High-density lipoprotein, CEC, and serum CLC will be analyzed as previously described (64–66). Additional information will be gained through the analysis of chylomicrons (67), HDL and LDL subfractions, lipoprotein transfer enzymes (Cholesteryl Ester Transfer Protein activity) (68), proprotein convertase subtilisin/kexin type 9 (PCSK9) (69), paraoxonase (PON-1) activity (70), serum amyloid A levels, GlycA (71), apolipoproteins AI and B (71), lipoprotein(a) (72), and oxidized phospholipids (73). The fatty acid profile in erythrocyte membranes will provide additional insights at the molecular level (74).

#### Metabolic pathways

An analysis of the metabolome in PBMCs will be performed using combinations of untargeted and targeted LC/MS approaches (2).

#### Sulfur signaling

To address the transsulfuration pathway, sulfur compounds (amino acids, thiosulfate, and H_2_S) will be analyzed in serum and urine at baseline, after three fasting days, at the end of fasting, as well as 1 month post food reintroduction (75).

#### DNA methylation profiling

Experimental surrogate indicators of biological age [so-called epigenetic aging clocks) will be analyzed using methylation arrays from blood DNA methylation (76)].

#### Gut microbiota composition

Stool samples will be collected for shotgun metagenomics to determine the fecal microbiota composition in all participants prior to fasting and from the first spontaneous stool after the fasting period as previously described (6). We will evaluate microbial composition by identifying species-specific marker genes and functional potential by profiling microbial metabolic pathways and other molecular functions as described in other published fecal microbiome studies (77). The study of carbohydrate metabolism will be complemented by a carbohydrate-active enzyme (CAZy) profiling method that is currently in development at european molecular biology laboratory (EMBL) Heidelberg. All raw microbial data will be made available on public repositories.

#### Clinical data

Clinical data (e.g., body weight, body-mass-index, systolic and diastolic blood pressure, and heart frequency) will be documented at baseline, during fasting and food reintroduction as well as 1 and 4 months afterward. The abdominal circumference will be measured before and after fasting. Changes in ketonuria, capillary ketonemia, and capillary blood glucose levels will be measured during the fasting period and food reintroduction. Nitrogen balance, measured in 24-h urine samples (15), will be determined at baseline and during the fasting and food reintroduction period in the MRI subgroup only.

A clinical standard laboratory blood profile will be measured in each blood sample, during the transition day and after fasting (10). Additional blood samplings will be obtained from the first 32 subjects after three fasting days as well as 1 month afterward.

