## Methods and analysis

### Aims

First, the GENESIS study aims to document changes in body composition and the contribution of the main metabolically active tissues (skeletal muscular tissues, adipose tissues, liver, heart, spleen, kidneys, and brain) to the metabolic switch during a 12-day fasting period. Changes in the size and mass of organs will be quantified. We hypothesize that a re-expansion and regeneration will follow a transient decrease of organ volume during fasting up to 4 months after food reintroduction. Protein resynthesis upon food reintroduction might correspond to an acceleration of the physiological protein turnover, which will be evaluated by measuring nitrogen excretion. Additionally, the organs’ specific compositions, especially the fat components, and their function will be documented along the fasting process. We hypothesize that these multi-system changes are safe, and that they could also be reflected by an improved cardiac and skeletal muscle metabolism and mitochondrial oxidative capacity which will be investigated by spiroergometry.

Second, the study focuses on fat storage, function, and exchange in adipose tissue, liver, spleen, kidney, and splanchnic tissue. Among the lipids studied, we focus on cholesterol metabolism during fasting, particularly sub-types of HDL, but also CEC and fatty acid profiles in the erythrocyte membrane.

Third, we will measure PBMC metabolome profiles to reveal cellular metabolic changes in circulating, easily accessible immune cells.

Fourth, we will determine whether persulfidation, which contributes to the maintenance of cellular oxidative functions, changes during fasting.

Last, we will measure if various metabolic and physiological changes, as described above, correlate to individual gut microbiota profiles. The composition and function of the fecal microbiota will be evaluated during LF using shotgun metagenomics. This will help us understand how intestinal microorganisms are linked to human physiology during fasting.

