### Fasting intervention

The subjects will receive a plant-based, organic calorie-restricted diet (600 kcal/day) 1 day before the study begins. The 12-day fasting period will be initiated by emptying the intestinal tract *via* the intake of a laxative [e.g., sodium sulfate (Glaubers’ Salt) in the morning or sodium picosulfate (Laxoberal^®^, Sanofi-Aventis, Germany) the night before]. During the fasting period, the energy intake is limited to 200–250 kcal/day (10), which will be achieved with 0.25 L freshly squeezed, organic fruit juice at noon, 0.25 L vegetable soup in the evening and 20 g honey. Participants will be asked to drink a minimum of 2 L of water or non-caloric, caffeine-free herbal teas that are purchased by certificated, organic companies (SONNENTOR Kräuterhandelsgesellschaft mbH, Sprögnitz, Austria; Ulrich Walter GmbH, Diepholz, Germany). Every second fasting day, the colon will be emptied by an enema or a laxative. On the last fasting day, plant-based organic food will be progressively reintroduced over 3–4 consecutive days (800–1,600 kcal/day).

Medical doctors and nurses will supervise the fasting intervention. An accompanying program consisting of physical exercise, mindfulness, and meditation will be provided and group interaction will be favored. The training program includes daily outdoor walks of 1.5 h, moderate-intensity fitness exercises and free access to the gym and swimming pool.

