#### Questionnaires

Several validated questionnaires will be recorded at baseline, at the end of fasting as well as 1 and 4 months afterward to document mental wellbeing (Warwick-Edinburgh Mental WellBeing Scale) (78), global health (PROMIS Scale) (79), physical activity (Godin Leisure-Time Exercise Questionnaire) (80), sleep quality (Pittsburgh Sleep Quality Index) (81), and dietary behavior (short healthy eating index survey) (82). Lifestyle habits like smoking behavior, alcohol consumption, or physical activity in hours/week will be self-reported. Participants will document energy level, emotional and physical wellbeing, as well as symptoms including fatigue, muscle weakness, back pain, hunger, anxiety, headache, and sleep disturbances on visual scales (0–10) at baseline, daily during fasting and food reintroduction as well as 1 and 4 months afterward.

Adverse events will be documented continuously.

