### Data analysis plan

The data of all clinical endpoints will be collected before and after 9 ± 3 fasting days. Demographic data and each participant’s medical history will be captured at baseline. The detailed timing of all measurements is shown in Table 2.

**TABLE 2 T2:** Summary of measurements.

	Before	Transition	Fasting days													Food reintroduction	+1 month	+4 months
Measurements	−5 to −2	−1	0	1	2	3	4	5	6	7	8	9	10	11	12			
Demographic data	x																	
Medical history	x																	
Anthropometric measurements	x	x	x	x	x	x	x	x	x	x	x	x	x	x	x	x	x	x
Vital signs	x	x	x	x	x	x	x	x	x	x	x	x	x	x	x	x	x	x
Blood sampling		x				x			x								x	
Capillary blood sampling	x	x	x	x	x	x	x	x	x	x	x	x	x	x	x	x		
First morning urine sampling			x			x			x								x	
24 h urine sampling	x		x	x	x	x	x	x	x	x	x	x	x	x				
MRI	x												x				x	
MRS P31 and H1	x												x				x	
Bioelectrical impedance analysis	x												x				x	
Quadriceps muscle ergometry	x												x				x	
Triaxial actigraphy	x		x	x	x	x	x	x	x	x	x	x	x	x			x	
Spiroergometry	x										x						x	
Stool sampling	x															x		
Visual scores: wellbeing, symptoms	x	x	x	x	x	x	x	x	x	x	x	x	x	x	x	x	x	x
Questionnaires and life style		x											x				x	x
Adverse events	x	x	x	x	x	x	x	x	x	x	x	x	x			x	x	x

Measurements only conducted in the first stage of this study (*n* = 32) are highlighted in blue.

Further, the Supplementary File contains a detailed description of the anthropometric data, vital signs, blood, urine and stool samples, the MRI and MRS acquisition protocols, bioelectrical impedance analysis, quadriceps muscle ergometry, triaxial actigraphy, and spiroergometry.

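### Table 2 schedules no 24-hour urine during food reintroduction, although the text plans nitrogen balance then and one of the aims relies on it

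*Protocol article*

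**What the plan says.** All references are to the protocol article.

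- **Aims:** "Protein resynthesis upon food reintroduction might correspond to an acceleration of the physiological protein turnover, which will be evaluated by measuring nitrogen excretion". The refeeding phase is thus the period of interest for this measurement.
- **Clinical data:** nitrogen balance, measured in 24-hour urine, "will be determined at baseline and during the fasting and food reintroduction period in the MRI subgroup only". The MRI subgroup is the 32 first-stage participants.
- **Data analysis plan:** "The detailed timing of all measurements is shown in Table 2". In that table the row "24 h urine sampling" is marked in the column before the fast and on days 0 to 11, and nowhere else.
- **Fasting intervention:** "On the last fasting day, plant-based organic food will be progressively reintroduced over 3–4 consecutive days".
- **Questionnaires**, on a secondary point: "Adverse events will be documented continuously". In Table 2 the row "Adverse events" is marked in every column except days 11 and 12.

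**The concern.** Resynthesis after a fast can be seen in nitrogen data only if nitrogen is measured after food returns. The text commits to that; the schedule table does not show it. Staff commonly work from the schedule table when they plan visits and sample kits. If they do so here, collection stops on day 11 and the comparison of refeeding with fasting loses one of its two sides. Refeeding urine that was not collected at the time cannot be obtained later, so the choice between text and table decides whether this part of the Aims has any data.

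**Working it through.** No power or sample-size figure is involved. The check is a column-by-column reading of Table 2 against the text.

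**1. Columns.** Before, Transition, days 0 to 12, Food reintroduction, +1 month, +4 months: 1 + 1 + 13 + 1 + 1 + 1 = 18.

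**2. The two rows.** Each has exactly 18 cells, so a simple shift of marks along the row is unlikely.

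| Row | Marked | Blank |
|---|---|---|
| 24-hour urine | Before; days 0–11 (1 + 12 = 13 of 18) | Transition, day 12, Food reintroduction, +1 month, +4 months |
| Adverse events | All other columns (16 of 18) | Days 11 and 12 |

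**3. Are the late columns in use?** Yes. Anthropometric measurements, vital signs, capillary blood and visual scores are all marked on days 11 and 12 and at Food reintroduction. Stool sampling is also marked at Food reintroduction.

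**4. Text against table for 24-hour urine.**

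| Period | Clinical data | Table 2 |
|---|---|---|
| Baseline | planned | marked |
| Fasting | planned | days 0–11 marked, day 12 blank |
| Food reintroduction | planned | blank |

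**5. Can another passage reconcile them?**

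- *Overlap at the end of the fast.* Food returns on the last fasting day. Taking day 12 as that day, as the table's labels suggest, the overlap supplies nothing, because day 12 is blank too. If day 0 were counted as the first of the twelve days, day 11 would be the last. At most one marked collection would then touch the first of the 3–4 reintroduction days, and 2–3 would remain unmarked.
- *Shorter fasts.* The Data analysis plan also speaks of endpoints "collected before and after 9 ± 3 fasting days", that is 6 to 12 days. In a participant who stopped at day 9, urine on days 10 and 11 would fall in refeeding. But nitrogen balance is confined to the MRI subgroup, and Study design gives that subgroup 12 fasting days.

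Neither passage removes the contradiction.

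**The case against.** Four points can fairly be made on the other side.

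**The text already plans the measurement.** A reader might infer from the table that the resynthesis question cannot be tested. The documents do not support that. Clinical data states the refeeding collection outright, Table 2 is captioned as a summary, and the Supplementary File, which is not at hand, describes the urine samples. The loss occurs only if the table prevails over the text. The Aims also word the turnover idea as a possibility. This objection stands against the stronger reading. It does not remove the mismatch: the article assigns timing to Table 2, and a supplement cannot make two incompatible schedules both true.

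**The blanks may come from the way the table was read.** A cell spanning several columns can appear as one mark followed by empty cells, and the 18-cell count does not exclude this. The explanation is plausible for the adverse-event row. The MRI and questionnaire rows show the same shape, a mark on day 10 and then blanks on days 11 and 12, although the text places both at the end of fasting. It is weaker for 24-hour urine, where the marks run singly through day 11 and nothing follows.

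**Adverse events.** A reader might infer that events on the two longest-fasted days go unrecorded and that this favours a finding of safety. Nothing supports that. The rule of continuous recording has no exception, and vital signs and symptom scores are marked on both days. Blank cells are not lost events.

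**Nitrogen intake.** A reader might also ask how intake enters the balance. A condensed article may leave that to its cited method and the fuller documents, so it is not a finding here.

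**Conclusion.** The point holds as a contradiction between text and table. Aims and Clinical data need 24-hour urine during food reintroduction; Table 2 marks it only before the fast and on days 0 to 11. If Table 2 is followed, the nitrogen-based evaluation of resynthesis has no refeeding measurement in any of the 32 first-stage participants. If the text is followed, nothing is lost and only the table is wrong.

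The conclusion rests on two assumptions: that the 24-hour urine row was read correctly from the published table, and that day 12 is the last fasting day in the MRI subgroup. It concerns this one evaluation and does not touch the MRI primary endpoints. The adverse-event row is a matter to check, and no claim of bias in the safety assessment follows from it.

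**What to change.** Reconcile the passages.

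- If refeeding urine is collected, as Clinical data plans, mark 24-hour urine in Table 2 on day 12 and at Food reintroduction for the 32 first-stage participants.
- If it is not collected, remove the nitrogen-based evaluation of resynthesis from the Aims and correct Clinical data to baseline and fasting only.
- If collection has already finished, state which schedule was followed.
- Check the adverse-event row in the published table. If days 11 and 12 are truly blank, mark them to agree with the rule of continuous recording.

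**Cost.** The table correction is editorial. The article does not say how many refeeding days would be sampled. If every one were, the extra load would be 3–5 collections per participant: 3–4 reintroduction days, plus day 12 if it is not already one of them. That is 32 × 3 = 96 to 32 × 5 = 160 collections, in people who already collect urine daily. Measured against the text, these are not additions, since it already plans them.

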#### Questionnaires

Several validated questionnaires will be recorded at baseline, at the end of fasting as well as 1 and 4 months afterward to document mental wellbeing (Warwick-Edinburgh Mental WellBeing Scale) (78), global health (PROMIS Scale) (79), physical activity (Godin Leisure-Time Exercise Questionnaire) (80), sleep quality (Pittsburgh Sleep Quality Index) (81), and dietary behavior (short healthy eating index survey) (82). Lifestyle habits like smoking behavior, alcohol consumption, or physical activity in hours/week will be self-reported. Participants will document energy level, emotional and physical wellbeing, as well as symptoms including fatigue, muscle weakness, back pain, hunger, anxiety, headache, and sleep disturbances on visual scales (0–10) at baseline, daily during fasting and food reintroduction as well as 1 and 4 months afterward.

Adverse events will be documented continuously.

### Data analysis plan

The data of all clinical endpoints will be collected before and after 9 ± 3 fasting days. Demographic data and each participant’s medical history will be captured at baseline. The detailed timing of all measurements is shown in Table 2.

**TABLE 2 T2:** Summary of measurements.

	Before	Transition	Fasting days													Food reintroduction	+1 month	+4 months
Measurements	−5 to −2	−1	0	1	2	3	4	5	6	7	8	9	10	11	12			
Demographic data	x																	
Medical history	x																	
Anthropometric measurements	x	x	x	x	x	x	x	x	x	x	x	x	x	x	x	x	x	x
Vital signs	x	x	x	x	x	x	x	x	x	x	x	x	x	x	x	x	x	x
Blood sampling		x				x			x								x	
Capillary blood sampling	x	x	x	x	x	x	x	x	x	x	x	x	x	x	x	x		
First morning urine sampling			x			x			x								x	
24 h urine sampling	x		x	x	x	x	x	x	x	x	x	x	x	x				
MRI	x												x				x	
MRS P31 and H1	x												x				x	
Bioelectrical impedance analysis	x												x				x	
Quadriceps muscle ergometry	x												x				x	
Triaxial actigraphy	x		x	x	x	x	x	x	x	x	x	x	x	x			x	
Spiroergometry	x										x						x	
Stool sampling	x															x		
Visual scores: wellbeing, symptoms	x	x	x	x	x	x	x	x	x	x	x	x	x	x	x	x	x	x
Questionnaires and life style		x											x				x	x
Adverse events	x	x	x	x	x	x	x	x	x	x	x	x	x			x	x	x

Measurements only conducted in the first stage of this study (*n* = 32) are highlighted in blue.

Further, the Supplementary File contains a detailed description of the anthropometric data, vital signs, blood, urine and stool samples, the MRI and MRS acquisition protocols, bioelectrical impedance analysis, quadriceps muscle ergometry, triaxial actigraphy, and spiroergometry.

### Sample size calculation

The required sample sizes vary between the outcome parameters. Previously, the effect size in matched subjects was 0.81 for T2 relaxometry in muscles (55). Using these assumptions, the minimal sample size requirement is 14 to detect meaningful acute changes in muscle physiology (alpha = 0.05, power = 0.80). MRS studies monitoring triglyceride (TG) content during CR (83, 84) observed that effect sizes were 1.09 and 0.59 in liver and muscle, respectively. Using the small effect size of muscle changes (alpha = 0.05, power = 0.80), the required sample size to detect organ-specific differences in MRS measurements is 28. To account for a potential drop-out rate of 15%, the sample size was set to 32.

Clinical routine laboratory examinations and other blood sample analyses will be performed on 100 samples. This number of participants was chosen to reach sufficient power for detecting differences in gut metagenome analysis. Large inter-individual differences are usually observed in the composition of fecal microbiomes. Small differences in alpha diversity (effect size 0.55) between two groups of 50 individuals can be detected with an 80% statistical power (85). Missing values are commonly encountered in fecal microbiome evaluations (85). Accounting for missing data and sufficient numbers to quantify bacteria abundance at the species level for at least 50 individuals, we estimated that 100 subjects are needed for this part of the study (power = 0.80). This is based on a fecal metagenome analysis, which included missing values for more than 50% of 612 bacterial species out of 724 species detected (86).

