### Study design

The GENESIS study is a prospective, monocentric, single-arm interventional study using a two-stage design. A total of 100 subjects will be included (Figure 2). The first 32 participants will undergo an augmented examination plan, including MRI/MRS scans to evaluate body composition changes at four time points: prior to and at the end of 12 fasting days, 1 and 4 months post fasting. This sub-cohort is statistically powered for detecting changes in whole body composition. Sixty-eight additional subjects will then be included for gut microbiota and lipid profile analyses. The study follows the STROBE guidelines (42).

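### The power statement behind the total of 100 is for two groups of 50 people, but the planned stool comparison is before versus after fasting in the same people

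*Protocol article*

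**What the plan says.** The section Sample size calculation says that 100 was chosen to give enough power for the gut metagenome analysis. It gets there in two steps.

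- **Power.** It cites one result from the literature: "Small differences in alpha diversity (effect size 0.55) between two groups of 50 individuals can be detected with an 80% statistical power". No alpha, sidedness or test is given for this sentence. The pair "alpha = 0.05, power = 0.80" appears only with the muscle and MRS calculations.
- **Missing data.** "Accounting for missing data and sufficient numbers to quantify bacteria abundance at the species level for at least 50 individuals", it continues, "we estimated that 100 subjects are needed for this part of the study (power = 0.80"). The allowance is drawn from an earlier metagenome study with "missing values for more than 50% of 612 bacterial species out of 724 species detected".

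Three other sections set out the comparison itself. Study design describes a "prospective, monocentric, single-arm interventional study using a two-stage design". Gut microbiota composition has stool collected "in all participants prior to fasting and from the first spontaneous stool after the fasting period". Statistical analysis plans a mixed model for repeated measures for quantitative variables. It also foresees subgroups by sex or by unsupervised clustering, without giving sizes.

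**The concern.** A calculation for two groups of people sets the difference against between-person variation in both groups. A before/after comparison in the same people sets the mean change against the standard deviation of the change, and that depends on the within-person correlation. The section itself notes that people differ widely in their faecal microbiome, which is the situation in which pairing matters most. Yet it gives neither a paired effect size nor a correlation.

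The same section sizes its muscle outcome from an effect size in matched subjects, so its first calculation respects the pairing and the one behind the total of 100 does not.

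What is at stake is how the alpha-diversity result will be read. Someone who takes 0.55 at 80% power as the sensitivity of the before/after test will have the wrong figure, most likely too pessimistic a one.

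**Working it through.** **Inputs.** From Sample size calculation: effect size d = 0.55, 50 per group, power 0.80, at least 50 evaluable individuals, total 100. Assumed: d is a standardised mean difference, and alpha is 0.05 two-sided (the article gives 0.05 elsewhere in the section and never states sidedness). The within-person correlation ρ is not given, so a range is shown.

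**1. The plan's own figure.** Two groups, normal approximation: power = Φ(d·√(n/2) − 1.96) = Φ(0.55 × 5 − 1.96) = Φ(0.79) = 78.5%. Required n = 2(1.96 + 0.84)²/0.55² = 52 per group. The noncentral t gives 77.7% and 53 per group. With d = 0.56 the power is 80.0% (normal) or 79.2% (t). The stated 80% is reproduced to about rounding.

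**2. From 50 to 100.** Reading the allowance as about half the values missing, 50/(1 − 0.5) = 100. The two-group sentence supplies the 50 and the missingness allowance supplies the doubling.

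**3. How the section treats its matched outcome.** A paired t-test at effect size 0.81, two-sided 0.05 and 80% power needs 14.0 subjects, which agrees with the stated 14.

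**4. The planned comparison.** For a paired t-test the effect size is dz = mean change / SD of change. If 0.55 is on the between-person scale with equal variances, dz = 0.55/√(2(1 − ρ)).

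| ρ (assumed) | dz | Pairs for 80% power | Power, 50 pairs | Power, 100 pairs |
|---|---|---|---|---|
| 0 | 0.39 | 54 | 76.9% | 97.1% |
| 0.25 | 0.45 | 41 | 87.5% | 99.4% |
| 0.5 | 0.55 | 28 | 96.8% | >99.9% |
| 0.7 | 0.71 | 18 | 99.8% | >99.9% |

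If 0.55 was instead meant as dz itself, the row for ρ = 0.5 applies, because √(2 × 0.5) = 1.

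**5. Detectable change.** By normal approximation, dz = (1.96 + 0.84)/√n, which is 0.396 for n = 50 and 0.280 for n = 100. The noncentral t gives 0.404 and 0.283, so 0.40 and 0.28. On the between-person scale these are multiplied by √(2(1 − ρ)). For 100 pairs that is 0.28 × 1.41 = 0.40 at ρ = 0 and 0.28 at ρ = 0.5.

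**The case against.** The best defence is that the sentence quotes a general result from the literature, and that "between two groups of 50 individuals" may loosely mean 50 samples before and 50 after. On that reading the calculation simply ignores the pairing. At ρ = 0 the two approaches nearly agree (76.9% against 77.7% by t), and beyond a trivially small positive correlation the paired test has more power. The participant number is therefore safe. The microbiome is also not the primary endpoint: that is body composition by MRI, and the 32-person stage has its own calculation. All of this stands, and it limits how serious the point is. It does not make the stated power a description of the planned test.

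A reader might infer more than the article supports in four ways.

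- **That 80% is an arithmetic error, the true figure being 78%.** The normal approximation gives 78.5%, an effect of 0.56 gives about 80%, and the sentence fixes no alpha, sidedness or test. A one-sided test would give about 86%. The gap is no more than rounding and choice of test.
- **That 100 is 2 × 50.** The article reaches 100 by the missing-data step.
- **That the study never compares groups of people.** Subgroups by sex or clustering are foreseen, but none is set at 50 against 50 or tied to alpha diversity or to the sample size.
- **That the study is too small, or that a null result could not be interpreted.** The table shows the opposite for size, and a confidence interval for the mean change can be read whatever the planning figure was.

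**Conclusion.** The point holds as a mismatch between the basis of the sample size and the design. The only power statement behind the total of 100 is for two groups of 50 people, while the defined stool comparison is paired. Neither the 80% nor the 0.55 is the sensitivity of that comparison.

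The mismatch probably errs on the safe side. With 100 complete pairs and ρ of 0 or more, power for 0.55 is at least 97%. With only 50 pairs it runs from about 77% at ρ = 0 to 99.8% at ρ = 0.7. These figures assume two-sided alpha 0.05, a standardised mean difference, equal variances before and after, and a t-test on a single measure. They do not cover species-level testing under false discovery rate control, where power would be lower. The article gives no ground for changing the number of participants.

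**What to change.** Replace the two-group sentence with a paired statement that names alpha and sidedness, for example:

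> With two-sided alpha 0.05 and 80% power, 100 participants with both samples can detect a within-person standardised mean change in alpha diversity (mean change divided by SD of change) of 0.28; for a measure such as a species quantifiable in only 50 participants at both times, the figure is 0.40 before false discovery rate correction.

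Keep the missing-data step as the reason for going from 50 to 100. Tie the 50 to species-level measures, as the section does, and not to loss of whole participants. If 0.55 is kept as the anticipated effect, say whether it is on the between-person scale or the scale of the change and, in the first case, state the assumed within-person correlation.

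The cost is rewording one section. Recruitment, sampling and analysis do not change.
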